## **8. Description of the conduct of the study**

### **8.1 Conventional management of iMN patient**

All adult patients with a nephrotic syndrome should receive symptomatic treatment. When the diagnosis of MN is confirmed by anatomopathology and/or serology (positive Anti-PLA2R antibodies), additional tests comprise scanner TAP, serologies (HBV, HBC), anti-nuclear and anti THSD7A antibodies. After 6 months of NIAT and a persistent nephrotic syndrome, an immunosuppressive therapy is started. They have a follow-up every 3 months.

### **8.2 Patient selection for this study**

Patients with clinical diagnosis of MN will be tested for the presence of PLA2R1-Ab according to local practices. The selection of the patients fulfilling the inclusion criteria will not delay the start of the symptomatic treatment according to KDIGO guidelines. If the patient meets the criteria for recruitment to the study, they will be informed of the study by the referring nephrologist. Full information will be supplied orally, together with written information.

### **8.3 Inclusion and randomization = M0**

After signing the study consent, participants will be randomized in one of the two treatment arms:

- GEMRITUX treatment
- Personalized treatment

Randomization will be balanced (1:1). Centralized block randomization will be conducted by the *Département de la Recherche Clinique et de l'Innovation* (DRCI) (Department of Clinical Research and Innovation) at CHU Nice (Nice University Hospital). Taking into account the size of our study

sample which is relatively small and the high number of participating centers, (which is high in light of the need to ensure that the intended level of recruitment is met), it does not seem appropriate to account for the center as a stratification parameter.

Randomization will be integrated in the electronic case report file (e-CRF) devised specifically for the study with Redcap® software. Using their personal access details to login, the investigator will provide the necessary patient information (i.e. the first letter of their first and last name and their month and year of birth) for random allocation to treatment by the online randomization module (Redcap®). Randomization can then take place around the clock. The treatment group and inclusion number for the patient will then be relayed to the investigator and the central lab team. The patient's trial records will then be created automatically, allowing data to be entered.

#### **8.4 Frequency of follow-up visit-protocol**

After randomization, all patients will be scheduled at M3, M6, M9, M12, M18 and M24 post-treatment for a routine follow-up, and benefit from a symptomatic antihypertensive and antiproteinuric treatment throughout the study period according to the KDIGO guidelines.

In the GEMRITUX group: at M6, if the patient exhibits an active disease (UPCR remains  $> 3.5$  g/g and albuminemia  $< 30$  g/l), they will receive two 375 mg/m^2 rituximab infusions at 1-week interval.

In the personalized group, rituximab injections should be scheduled between 5 and 14 days after randomization in case the epitope results are in favor for immunosuppressive treatment, as follows:

- at M0 and M6, if the patient exhibits anti-PLA2R1 anti-CTLD1 or CTLD7 activity, they will receive two 1 g infusions at 2-week interval.
- At M6, if a patient has an active disease/ anti-PLA2R1 ab + or if he has an active disease /anti-PLA2R1 Ab –, symptomatic treatment should be optimized. And if he exhibits anti-CysR restricted activity with active disease (UPCR remains  $> 3.5$  g/g and albuminemia  $< 30$  g/l), they will receive two 375-mg/m^2 rituximab infusions at 1-week interval.

[figure not shown]

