## 2. Study objectives

### 2.1 Primary objective

Our main objective is to compare the efficacy of a **personalized treatment** of nephrotic iMN driven by anti-PLA2R1 antibody epitope profile at month 0 and month 6 to induce clinical remission (partial or complete) of the nephrotic syndrome at month 12:

- Restricted anti-CysR activity at month 0: 6-month symptomatic treatment
- Restricted anti-CysR activity at month 6 after symptomatic treatment and if the nephrotic syndrome persists at month-6 (UPCR remains  $> 3.5$  g/g and albuminemia  $< 30$  g/l): two 375 mg/m^2 rituximab infusions at 1-week interval

- Anti-CTLD1/7 activity at month 0 or month 6: two 1g rituximab infusions at 2-week interval at month 0 and/or month 6

with the GEMRITUX protocol: 6 months of symptomatic antihypertensive and antiproteinuric therapy, and if the nephrotic syndrome persists at month-6 (UPCR remains > 3.5 g/g and albuminemia < 30 g/l), two 375 mg/m^2 infusions at 1-week interval. For patients who will develop anti-rituximab antibodies, treatment with human anti-CD20 is widely recommended.

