#### **M6 visit = 6 months after randomization +/-15 days**

- Consultation date
- Clinical examination: weight, blood pressure, edema
- Serious adverse events
- Changes in concomitant treatments
- Blood and urine lab results
- Estimated GFR CKD EPI
- Centralized assays for both arms:
  - 2 dry tubes of 5 ml of blood and 2 EDTA tubes of 3 ml of blood will be shipped to Nice at room temperature for PLA2R1-Ab, epitope profile determination, serum rituximab levels, anti-rituximab antibodies, and, B and T cells counts (see manual lab)
- **In the GEMRITUX arm**
  - If disease still active (UPCR remains > 3.5 g/g and albuminemia < 30 g/l): plan two 375 mg/m^2 Rituximab infusions at 1-week interval (+/- 2 days) between 5 and 14 days after M6 visit.
  - If remission (partial or complete, see p.12): symptomatic treatment to be continued.
- **In the personalized arm/ Patients who received RTX at M0**
  - If remission (partial or complete, see p.12): symptomatic treatment to be continued alone and contraception will be required during 12 months after the end of the treatment.
  - If disease still active / Restricted anti-CysR activity: plan two 375 mg/m^2 rituximab infusions at 1-week interval (+/- 2 days) between 5 and 14 days after M6 visit.

- if disease still active / Anti-CTLD1/7 activity: plan two 1g rituximab infusions at 2-week interval (+/- 2 days) between 5 and 14 days after M6 visit. For patient who will develop anti-rituximab antibodies, treatment with human anti-CD20 is widely recommended.

*NB: If the patient still active disease / anti-PLA2R1 Ab-; the symptomatic treatment should be optimized*

- **In the personalized arm/ Patients who received 6-month symptomatic treatment**

- If remission (partial or complete, see p.12): symptomatic treatment to be continued
- If disease still active / Restricted anti-CysR activity: plan two 375 mg/m^2 rituximab infusions at 1-week interval between 5 and 14 days after M6 visit.
- if disease still active / Anti-CTLD1/7 activity: plan two 1g rituximab infusions at 2-week interval between 5 and 14 days after M6 visit.

**For all:** plan M9 +/-15 days and hand out a prescription to the patient for blood and urine analyses\*

\* Blood sample: urea, creatinine, electrolytes (sodium, potassium, chloride, bicarbonate), protein, albumin, full blood count.

Spot morning urine sample: protein, albumin, urea, creatinine.

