### **At the first relapse**

If the patient presents a still active disease with anti-PLA2R1 and anti-rituximab activity, the following cares are left to the investigator's discretion due to the Rituximab contraindication. However, the patient must perform the following visits according to the protocol.

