## **9.3 Concomitant Treatments**

### **- Prohibited and/or Restricted Treatments**

Immunosuppressive agents or immunosuppressive doses of systemic corticosteroids are prohibited during the study (unless utilized to treat a drug related adverse event).

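### Month-6 retreatment rule is contradictory for personalized-arm patients in remission with persisting CTLD1/7 activity: section 8.4 retreats them, the 8.5 visit text does not

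*Protocol*

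**What the plan says.** **Unconditional on disease activity.** Section 8.4, for the personalized group: "at M0 and M6, if the patient exhibits anti-PLA2R1 anti-CTLD1 or CTLD7 activity, they will receive two 1 g infusions at 2-week interval". Section 2.1 gives the 1 g course for CTLD1/7 activity at month 0 or month 6, also without a disease-activity condition.

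**Conditional on disease activity.** The Summary (experimental plan) and section 1.3 attach persisting nephrotic syndrome or active disease to the month-6 course. The month-6 visit in 8.5 does so too: "if disease still active / Anti-CTLD1/7 activity: plan two 1g rituximab infusions at 2-week interval (+/- 2 days) between 5 and 14 days after M6 visit". For a patient who received rituximab at month 0 and is in remission at month 6, 8.5 says: "symptomatic treatment to be continued alone and contraception will be required during 12 months after the end of the treatment".

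**Human anti-CD20.** Section 2.1 says: "For patients who will develop anti-rituximab antibodies, treatment with human anti-CD20 is widely recommended". The Summary and the month-6 visit carry nearly the same sentence. Section 9.3 says: "Immunosuppressive agents or immunosuppressive doses of systemic corticosteroids are prohibited during the study", except to treat a drug-related adverse event. Under the heading on first relapse, for active disease with anti-rituximab activity, "the following cares are left to the investigator's discretion due to the Rituximab contraindication".

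**Month-6 categories.** Active disease means UPCR above 3.5 g/g and albumin below 30 g/L. Partial remission means UPCR below 3.5 g/g with a fall of more than 50%, plus albumin and creatinine conditions.

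**The concern.** The treatment strategy is itself the intervention under test, and the month-6 decision is its second and last step before remission is assessed at month 12. The epitope profile is measured in every patient at month 6, so each site will face this decision with the result in hand. If two sections direct opposite actions for the same patient, rituximab exposure in the experimental arm depends on which page the site follows. The safety comparison then mixes two exposure patterns. The per-protocol analysis announced in 12.1 has no single month-6 standard to judge adherence by. A published description of the strategy would also be unclear about what was given to patients already in remission.

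**Working it through.** **1. The plan's own figure.** The protocol gives no count of patients affected. The nearest stated figure is the 80% remission expected in the personalized arm (section 7.1). Reading the 40% there as applying to patients not already in spontaneous remission:

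0.30 × (0.50 + 0.50 × 0.40) + 0.70 × 0.85 = 0.210 + 0.595 = 0.805.

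This reproduces 80%. The 85% term comes from cohorts given repeated high-dose pulses, so the planning rate rests partly on a pattern of retreatment, which is what 8.4 and 8.5 define differently.

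**2. The rules side by side** (personalized arm, CTLD1/7 activity present at month 6):

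| Place in protocol | Disease active | In remission |
|---|---|---|
| 2.1 | 1 g course | 1 g course |
| 8.4 | 1 g course | 1 g course |
| Summary | 1 g course | none provided for |
| 1.3 | 1 g course | none provided for |
| 8.5, month-6 visit | 1 g course | symptomatic treatment continued |

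The middle column agrees throughout; the right-hand column does not.

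**3. Is the missing condition just shorthand?** Probably not safely so. In both 2.1 and 8.4 the line for CysR-restricted patients spells out the UPCR and albumin thresholds, while the CTLD1/7 line in the same list has none. Section 1.3 does not settle it: its condition is worded for patients coming off symptomatic treatment, and it closes by saying that all patients are re-evaluated serologically at month 6 and retreated under the same protocol.

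**4. Size.** Inputs: 64 patients randomized 1:1 (7.2, 8.3), so 64 / 2 = 32 personalized; 70% with CTLD1/7 activity (7.1); 64% six-month remission on the high dose in such patients (1.3).

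- CTLD1/7 at month 0: 32 × 0.70 = 22.4
- In remission at month 6: 22.4 × 0.64 = 14.3, or 14.3 / 32 = 45% of the arm
- In conflict: 14.3 × q, where q is the share of these whose CTLD1/7 activity persists

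The protocol does not give q, so the count runs from 0 (q = 0) to about 14 (q = 1). The ceiling is not sensitive to the inputs: with 29 evaluable patients it is 29 × 0.70 × 0.64 = 13.0, and with the 68.4% month-6 remission of the Nice cohort (1.3, all epitope profiles) it is 22.4 × 0.684 = 15.3. The count covers persisting activity only. A CysR-restricted patient who acquires CTLD1/7 activity while in remission would meet the same conflict, and no rate is given for that.

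**5. Patients in neither month-6 category.** UPCR falling from 6.0 to 3.2 g/g is a fall of (6.0 − 3.2) / 6.0 = 47%: not above 3.5, and not a fall of more than 50%. UPCR 4 g/g with albumin 31 g/L is neither active nor in remission. The month-6 visit in 8.5 has no branch for either patient.

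**The case against.** The strongest reply is that the conflict is confined to one cell. The month-0 rule is consistent, and the doses for active patients at month 6 agree across all sections. The 8.5 visit text is the most detailed and a site would probably follow it. Patients in this cell are already in remission, so a further course could change their month-12 status mainly through relapse, and the primary analysis is by intention to treat, so nobody leaves it. Section 1.3 also cites antibody depletion at month 6 as a strong predictor of remission, which suggests that fewer than 14 would be affected. All of this limits the size and stands. It does not remove the conflict: no text gives 8.5 precedence, and 1.2 acknowledges that antibodies may persist during apparent remission. A figure follows 8.4 and is not reproduced in the public text; whatever it shows, the conflicting sentences remain.

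Three stronger readings are tempting and are not supported.

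- A reader might take the 8.4 sentence beginning "At M6, if a patient has an active disease/ anti-PLA2R1 ab + or if he has an active disease" to withhold rituximab from active, antibody-positive patients. It does not. Optimizing symptomatic treatment is additional there, since the same list still gives rituximab for CTLD1/7 activity and for active CysR-restricted disease.
- A reader might say that human anti-CD20 is expressly banned. Section 9.3 does not name it, and read literally the class wording would also catch rituximab. The supportable point is a missing exception: section 9.1 lists only rituximab as study treatment, so 9.3 leaves the status of human anti-CD20 unclear. The discretion allowed at first relapse is compatible with a recommendation, but adds a third wording.
- A reader might treat the uncovered categories as a further contradiction. For control patients and CysR-restricted patients the rituximab trigger is simply not met, and symptomatic treatment continues by default. Only with CTLD1/7 activity do 8.4 and 8.5 again diverge.

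**Conclusion.** The month-6 rule for CTLD1/7 activity is wrong as written and has to be reconciled. Sections 8.4 and 2.1 direct a course that 8.5 withholds from a patient in remission, and the Summary and 1.3 side with 8.5 on requiring active disease. The size is 0 to about 14 of 32 personalized-arm patients, on the protocol's 70% and 64% and with the persistence of CTLD1/7 activity unknown. The clearest consequences are for rituximab exposure, the safety comparison and any judgement of adherence; the effect on month-12 remission cannot be quantified from the protocol. It would go too far to infer that the tested strategy as a whole is undefined, because the month-0 rule and the treatment of active patients at month 6 are consistent. The unclear status of human anti-CD20 under 9.3 and the uncovered month-6 categories are secondary.

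**What to change.** Replace the competing texts with one month-6 rule per arm, whose categories are mutually exclusive and cover every patient, including those who are neither active nor in remission as defined. Make the Summary, 1.3, 2.1, 8.4, the 8.5 month-6 visit and the first-relapse paragraph either repeat that rule or refer to it. State in 9.3 how the prohibition applies to human anti-CD20. Which patients are retreated, and with what, is for the investigators to decide; the need is only that the passages agree.

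The cost is a protocol amendment confined to wording, with no added visits, samples or patients. The exact per-protocol definition and any supportive analysis around other immunosuppressants can be left to the statistical analysis plan once the rule is fixed. The protocol already requires all concomitant medication to be recorded (9.3).

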| 
Randomized, open label, multicentre (22 centres), prospective trial comparing the efficacy of two therapeutic strategies to obtain clinical remission 1 year after diagnosis of iMN with nephrotic syndrome and anti-PLA2R1 antibodies:
 
 
- GEMRITUX protocol: 6 months of symptomatic antihypertensive and antiproteinuric therapy, and if the nephrotic syndrome persists at month-6 (urinary protein/creatinine ratio (UPCR) remains > 3.5 g/g and albuminemia < 30 g/l), two 375 mg/m^2 rituximab infusions at 1-week interval.
 
- Personalized treatment: 
 
o restricted anti-CysR activity at inclusion: 6-month symptomatic antihypertensive and antiproteinuric treatment (KDIGO)
 
o restricted anti-CysR activity after 6 months of symptomatic treatment with persisting nephrotic syndrome (UPCR remains > 3.5 g/g and albuminemia < 30 g/l): two 375 mg/m^2 rituximab infusions at 1-week interval;
 
o Anti-CTLD1/7 activity at inclusion or after 6 months with persisting nephrotic syndrome (UPCR remains > 3.5 g/g and albuminemia < 30 g/l): two 1g rituximab infusions at 2-week interval at month 0 and/or month 6. For patients who will develop anti-rituximab antibodies, treatment with human anti-CD20 is widely recommended.
 
 
 
 |

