## 1.2 Epitope Spreading as prognosis biomarker

Our first objective is to better select patients who will benefit from immunosuppressive treatment. Although the identification of PLA2R1-Ab has been paradigm shifting in the diagnosis and management of patients, there are outliers who call for additional biomarkers. Indeed, antibodies may persist during apparent clinical remission and conversely a drop in antibody titer may not be associated with a clinical remission (14, 19, 20).

PLA2R1 is a 180-kDa membrane receptor with a large extracellular region comprising 10 distinct globular domains including a cysteine-rich domain (CysR), a fibronectin type II domain (FNII), and 8 distinct C-type lectin domains (CTLD1-8) (21). Each domain is separated by a small linker sequence of about 10 amino acids. An immunodominant epitope was first identified in a region spanning the CysR-FNII-CTLD1 domains (22), which was further restricted to the CysR domain alone (23). In a first study, we identified reactive epitopes in the CysR, CTLD1 and CTLD7 domains, and that all samples reacted with CysR domain confirming that CysR was the immunodominant epitope. We further showed that patients with anti-CysR-restricted activity were younger, had lower proteinuria, and exhibited a higher rate of spontaneous remission and lower rates of renal failure progression (24). Conversely, high PLA2R1-Ab activity and epitope spreading beyond the CysR epitope were

independent risk factors of poor renal prognosis in a collection of 69 sera from five French nephrology centers.

In a second prospective trial we analyzed the predictive value of epitope-specific PLA2R1-Ab titer and epitope spreading at diagnosis in the 58 PLA2R1-Ab positive patients from GEMRITUX randomly allocated to rituximab plus NIAT (n=29) or NIAT (n=29). In adjusted analysis, epitope spreading at baseline was associated with a decreased remission rate at month 6 (OR, 0.16; 95% CI, 0.035 to 0.72;  $p=0.0171$ ) and last follow-up (median, 23 months; OR, 0.14; 95% CI, 0.03 to 0.64;  $p=0.0107$ ), independently from age, gender, baseline PLA2R1-Ab level and treatment group (Seitz-Polski et al. JASN Accepted august 2017).

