***We concluded that:***

- ***early remission rate depends on rituximab dosing,***
- ***low dose of rituximab could be enough for patients with anti-PLA2R1 activity restricted to CysR,***
- ***high dose of rituximab may be required for patients with epitope spreading.***

We will compare two therapeutic strategies in PLA2R1-related iMN patients to induce clinical remission of the nephrotic syndrome at month 12:

1. The strategy validated in the GEMRITUX protocol: 6 months of symptomatic antihypertensive and antiproteinuric therapy, and if the nephrotic syndrome persists at month 6 (UPCR remains > 3.5 g/g and albuminemia < 30 g/l), two 375 mg/m^2 infusions at 1-week interval.

2. A personalized strategy driven by the PLA2R1-Ab epitope profile at month 0 and month 6:

- Patients with restricted anti-CysR activity at month 0: these patients have a spontaneous remission rate under NIAT from 43% to 50% at month-6. We propose a symptomatic antihypertensive and antiproteinuric treatment for 6 months;
- Patients with restricted anti-CysR activity and persisting active disease at month 6 after symptomatic treatment (UPCR remains > 3.5 g/g and albuminemia < 30 g/l): in GEMRITUX, these patients have a high rate of remission with low dose of rituximab (about 70%). We propose two 375 mg/m^2 rituximab infusions at 1-week interval;
- Patients with anti-CTLD1/7 activity at month 0 or month 6 with persisting active disease after symptomatic treatment (UPCR remains > 3.5 g/g and albuminemia < 30 g/l): these patients have a very low rate of spontaneous remission under NIAT (from 0.05% to 17%) or under low dose of rituximab: in GEMRITUX 24% of remission at 6-month vs 64% with high dose of rituximab p=0.04. We propose to treat these patients with high dose of rituximab (two 1g rituximab infusions at 2-week interval at month 0 and/or month 6).

Ruggenti et al. demonstrated on a cohort of 81 consecutive iMN patients with PLA2R1-Ab that PLA2R1-Ab depletion 6 months post-rituximab strongly predicted remission (HR, 7.90; 95% CI, 2.54 to 24.60; P<0.001) (32). We will reevaluate the serologic status of all patients at month-6 and retreat according to the same protocol.

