## 9. Treatment

### 9.1 Study treatment

#### - Investigational Product

The investigational product rituximab will be stored in a secure area according to local regulations. It will be the responsibility of the investigator to ensure that investigational product is only

dispensed to study subjects. The investigational product will be dispensed only from official study sites by authorized personnel according to local regulations.

Rituximab will be delivered at two different doses according to the arm of the protocol: 1g J0 and J15 in the personalized arm with anti-CTLD1/7 activity or 375 mg/m^2 J0 and J7 in the personalized arm with anti-CysR activity and active disease at M6 or in the GEMRITUX arm with active disease.

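### Sections 2.1 and 8.4 retreat CTLD1/7-positive patients at M6 with two 1 g rituximab infusions whether or not disease is active; the M6 visit instruction retreats only active disease

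*Protocol*

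**What the plan says.** The protocol states the M6 rule for personalised-arm patients with CTLD1/7 activity in several places.

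**Serology alone**
- Section 8.4: "at M0 and M6, if the patient exhibits anti-PLA2R1 anti-CTLD1 or CTLD7 activity, they will receive two 1 g infusions at 2-week interval".
- Section 2.1, which defines the experimental strategy within the primary objective: "Anti-CTLD1/7 activity at month 0 or month 6: two 1g rituximab infusions at 2-week interval at month 0 and/or month 6".

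**Serology plus active disease**
- Section 8.5, M6 visit: "if disease still active / Anti-CTLD1/7 activity: plan two 1g rituximab infusions at 2-week interval". This applies both to patients given rituximab at M0 and to those given six months of symptomatic treatment. For those treated at M0 the remission branch reads: "If remission (partial or complete, see p.12): symptomatic treatment to be continued alone". Patients who had symptomatic treatment only also continue it when in remission.
- Summary, experimental plan: "Anti-CTLD1/7 activity at inclusion or after 6 months with persisting nephrotic syndrome".
- Section 1.3, description of the personalised strategy: "Patients with anti-CTLD1/7 activity at month 0 or month 6 with persisting active disease after symptomatic treatment".

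**Dose without visit or clinical condition**
- Section 9.1 assigns "1g J0 and J15 in the personalized arm with anti-CTLD1/7 activity". In the same sentence it ties the 375 mg/m² dose to active disease.

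**The concern.** These are two different treatment rules for the same patient, and the protocol does not say which prevails. The patient in question is in partial or complete remission at M6 but still has CTLD1/7 activity. Under Sections 2.1 and 8.4 that patient receives two 1 g infusions; under Section 8.5 the patient receives none.

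Three things are at stake.

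- **Safety.** A remitter already given 2 g at M0 would receive a second 2 g course without active disease. Section 5 lists infections among the most frequent serious reactions to rituximab.
- **The strategy under test.** The trial compares strategies across 22 or 23 sites (the protocol gives both figures). If sites follow different sections, the personalised arm is not one strategy.
- **Downstream analyses.** Rituximab exposure around M6 feeds the between-arm comparison of severe infections (Section 12.3.2) and the analysis of relapse between M12 and M24 (Section 3). It also determines who adhered to treatment for the per-protocol analysis (Section 12.1).

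**Working it through.** No sample size, power or alpha figure of the plan is in dispute, so there is none to reproduce. The check has two parts: a comparison of the rules, and a sizing of the affected group.

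**1. The rules compared**

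| Place | CTLD1/7 activity needed at M6 | Active disease needed at M6 | Remitter still CTLD1/7-positive at M6 |
|---|---|---|---|
| Section 2.1 | yes | not stated | 2 × 1 g |
| Section 8.4 | yes | not stated | 2 × 1 g |
| Section 8.5, M6 visit | yes | yes | no rituximab |
| Summary | yes | yes | no rituximab |
| Section 1.3 | yes | yes | no rituximab |
| Section 9.1 | yes (dose only, no visit named) | not stated | not settled |

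The missing condition in Sections 2.1 and 8.4 does not read as shorthand. Both sections state the clinical condition (UPCR > 3.5 g/g and albuminemia < 30 g/l) for the neighbouring 375 mg/m² branch. A reader would take its absence from the 1 g branch as deliberate. Section 2.1 also describes the strategy as driven by the epitope profile at both time points, so retreatment on serology alone is a plausible reading.

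**2. Cumulative dose for a remitter treated at M0**

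- Section 8.5: 2 × 1 g = 2 g.
- Section 8.4: 2 × 1 g + 2 × 1 g = 4 g. By the timing in Section 8.5, the second course would start 5 to 14 days after the M6 visit.

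**3. Size of the affected group**

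Inputs:
- 64 patients, randomised 1:1 (Sections 7.2 and 8.3).
- About 70% with CTLD1/7 activity (Section 7.1).
- 64% remission at six months with high-dose rituximab in such patients (Section 1.3).

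Steps:
- Per arm: 64 / 2 = 32.
- CTLD1/7-positive at M0: 32 × 0.70 = 22.4.
- Of these, in remission at M6: 22.4 × 0.64 = 14.3. With the 68.4% seen in the whole Nice cohort (Section 1.3): 22.4 × 0.684 = 15.3.
- Still CTLD1/7-positive in remission: share not given, assumed 10% to 50%. 14.3 × 0.10 = 1.4 and 14.3 × 0.50 = 7.2.
- As a share of the arm: 1.4 / 32 = 4.5% and 7.2 / 32 = 22.4%.

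With no assumption about the share, the count can lie anywhere from 0 to about 15. Two further groups could add to it. One is CysR-restricted patients in remission whose antibodies have spread to CTLD1/7 by M6. The other is patients neither in remission nor active as defined, for example with UPCR above 3.5 g/g but albumin of 30 g/l or more.

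**The case against.** The strongest reply is that Section 8.5 settles the matter in practice. It is the only place that says what to do with a patient in remission at M6, it is the text a site uses at the visit, and the Summary and Section 1.3 carry the same condition. Section 8.4 merges M0 and M6 in one bullet, and at M0 every patient is nephrotic by inclusion, so the condition may simply have been lost in compression. This makes it likely that many sites would follow Section 8.5. It does not remove the conflict: Section 8.4 names M6 expressly, Section 2.1 defines the experimental arm, and no clause ranks the sections.

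Several narrower points stand.
- Section 9.1 pairs doses with profiles and names no visit for the 1 g dose. It needs aligning but is weak evidence of a retreatment rule.
- Section 1.2 remarks that "antibodies may persist during apparent clinical remission", but this concerns PLA2R1 antibodies in general. It makes a CTLD1/7-positive remitter plausible without showing how common one is after 2 × 1 g.
- Section 1.3 reports that antibody depletion six months after rituximab strongly predicts remission (HR 7.90), which favours the low end of the assumed range.
- The 10% to 50% share has no source in the protocol. One or two patients would hardly move the safety or relapse results.

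The figure at the end of Section 8.4 is not available in the text reviewed. It may show a remission branch, but it could not reconcile the written rules.

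**Conclusion.** The concern holds: Sections 2.1 and 8.4 are wrong as written, if the M6 visit instruction reflects the intended strategy. Followed literally, they give a second 2 g course to patients in remission, which Section 8.5 withholds.

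About 1 to 7 of 32 personalised-arm patients would be affected, more likely near 1. This rests on the protocol's 70% and 64% and on the assumed 10% to 50% with persisting CTLD1/7 activity. The effect on the intention-to-treat comparison at M12 is limited to relapse between M6 and M12 in a few patients. The case for correction rests on avoidable exposure, on having one strategy across sites, and on a clear definition of adherence. It should be fixed, but it does not threaten the primary analysis.

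**What to change.** Make the M6 scheme in Section 8.5 the single governing rule and align the rest to it.

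- **Sections 2.1 and 8.4.** Split the CTLD1/7 branch by visit. At M0, two 1 g infusions on CTLD1/7 activity. At M6, two 1 g infusions only with CTLD1/7 activity and active disease (UPCR > 3.5 g/g and albuminemia < 30 g/l).
- **Section 9.1.** Limit the 1 g dose to M0, or to M6 with active disease.
- **Section 8.4.** State that the Section 8.5 scheme governs. In the same edit, clarify the second bullet, which opens by calling for optimised symptomatic treatment in active disease whether antibodies are present or absent.
- **Section 8.5.** Repeat the numerical definition of active disease in the personalised-arm branches, where it is not restated.
- **Per-protocol set.** Define adherence at M6 by this scheme.

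If retreatment on serology alone is what the sponsor intends, the Summary, Section 1.3 and Section 8.5 must change instead, with a justification for treating patients in remission.

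The cost is a wording amendment and a letter to sites, with ethics committee and agency approval if the change is judged substantial (Section 16.4). No extra patients, visits or assays are needed.
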